## Abstract

**Background:**

Gastroesophageal reflux disease lowers the quality of life and increases medical costs. Electroacupuncture has been used to ease symptoms and improve gastrointestinal motility in patients with gastroesophageal reflux disease. The main purposes of this study are to evaluate the efficacy and safety of this procedure.

**Methods/design:**

This is a protocol for a randomized, patient-blinded, assessor-blinded, sham-controlled trial. Sixty participants with symptoms of gastroesophageal reflux disease, who have previously undergone standard treatment, will be recruited from August 2015 at Kyung Hee University Korean Medicine Hospital. The participants will be allocated to either the electroacupuncture (n = 30) or the sham electroacupuncture group (n = 30); the allocation will be concealed from both the participants and the assessors. The EA group will undergo penetrating acupuncture at 18 fixed points and two optional points chosen using the pattern identification for gastroesophageal reflux disease. Electrical stimulation will be applied at some of the acupoints. The sham electroacupuncture group will undergo nonpenetrating acupuncture without electrical stimulation at 18 nonspecific points, each of which will be only 2 cm away from the true acupoints used in the electroacupuncture group. In both groups, the procedure will be performed using the Park device. The treatment will last for 6 weeks (with two sessions each week), and the outcome will be evaluated at baseline, 3 weeks, and 6 weeks. The primary outcome will be the proportion of responders with adequate symptom relief, whereas the secondary outcomes will comprise the results of the Nepean dyspepsia index; the Korean gastrointestinal symptom rating scale; the EQ-5D™; levels of gastrin, motilin, and inflammatory cytokines; the perceived stress scale; the qi-stagnation questionnaire; the patient global impression of change; and the spleen qi deficiency questionnaire.

**Discussion:**

The results of this trial will provide information about the efficacy and safety of electroacupuncture in the treatment of gastroesophageal reflux disease symptoms, as well as evidence regarding the use of electroacupuncture to treat gastroesophageal reflux disease in real clinical practice.

**Trial registration:**

Clinical Research Information Service Identifier, KCT0001653. Registered on 12 October 2015.

**Electronic supplementary material:**

The online version of this article (doi:10.1186/s13063-016-1371-8) contains supplementary material, which is available to authorized users.

## Background

Recently, the prevalence of gastroesophageal reflux disease (GERD) in Asia has been increasing, and GERD has now become an important disease [1–3]. Most patients with GERD require long-term therapy, as it is a chronic condition [4]. The standard treatment for GERD is known as a proton pump inhibitor (PPI), which heals the esophageal mucosa and eases the symptoms of GERD; the PPI has become a mainstay of GERD treatment [5]. However, approximately 20 % to 30 % of GERD patients continue to experience symptoms despite PPI treatment [6].

For this reason, interest is growing in complementary and alternative medicine—including acupuncture [5]. Recently, acupuncture has been reported to possibly ease gastrointestinal symptoms [7] and improve esophageal motility [8]. For instance, according to several previous animal studies [9–11], electroacupuncture (EA) increases abnormally low esophageal sphincter pressure (ESP) and reduces the frequency of transient lower esophageal reflux relaxations (TLESRs); in so doing, the treatment increases esophageal motility. GERD usually develops because of a decrease in ESP and the esophageal clearance capacity, as well as an increase in TLESR frequency [12]. Taken together, EA likely ameliorates GERD by controlling esophageal motility. However, little has been reported regarding the efficacy of EA in GERD; to our knowledge, no randomized controlled trials (RCTs), where a control group undergoes a sham procedure, have been carried out to evaluate the effect of EA on GERD in humans.

On another note, both gastrin and motilin are related to ESP, yet the influence of EA on the levels of these proteins has been disputed in previous studies [11, 13–16]. Therefore, with a view to resolving this controversy, we will evaluate the differences in gastrin and motilin levels after EA. Meanwhile, one report has stated that inflammatory mediators are associated with esophageal motility in patients with GERD [17]. For this reason, before and after treatment, we will test for several inflammatory cytokines present in GERD to evaluate the influence of EA on the levels of these cytokines.

In clinical practice, many patients who continue to suffer symptoms of GERD despite standard treatments turn to traditional Korean medicine—specifically EA. Nonetheless, there remains insufficient evidence from well-designed RCTs to support EA use. Hence, we have designed this trial to evaluate the efficacy and safety of partially individualized EA in patients with GERD who have already undergone standard therapy (PPIs or lifestyle modification). In the trial, an EA group will be compared with a sham EA control group. In addition, we will clarify the influence of EA on gastrointestinal (GI) hormones and inflammatory cytokines in patients with GERD.

## Methods/design

This protocol was prepared according to the Standard Protocol Items: Recommendations for Interventional Trials (SPIRIT) 2013 statement. See Additional file 1 for the completed SPIRIT checklist.

### Hypothesis

Partially individualized EA treatment is superior to sham EA in terms of easing the symptoms of GERD.

### Design

A single-center, parallel, randomized, patient-blinded, assessor-blinded, sham EA-controlled trial will be conducted at the Kyung Hee Korean Medicine Clinical Trial Center, which is affiliated with Kyung Hee University Korean Medicine Hospital in Seoul, Republic of Korea, from August 2015 to January 2016. Figure 1 shows the planned timeline of the trial.

**Fig. 1 Fig1:**
[figure not shown]
Timeline of the study

### Inclusion and exclusion criteria

Participants will (1) be ages 19 to 75 years; (2) have been diagnosed with GERD (either erosive or nonerosive) no more than a year before the trial begins; (3) have had one or more of certain GERD symptoms in the month before the trial begins (heartburn, regurgitation, dyspepsia, epigastric pain, belching, nausea, globus (feeling of a lump in the esophagus), dysphagia, coughing, or hoarseness [18]); (4) have had these symptoms on more than 4 days (in the case of mild symptoms) or more than 2 days (in the case of moderate and severe symptoms) during the 7 days before the trial begins; (5) have continued to experience the symptoms stated above despite standard treatment for GERD—using either medication or lifestyle modification, or both—for 4 weeks during the year before the trial begins; and (6) agree to participate in this study, voluntarily signing a written informed consent form. Symptoms that are easily tolerated, with minimal discomfort not affecting normal activities, are defined as “mild”; those that are sufficient to affect normal activities are classified as “moderate,” and severe symptoms comprise those that markedly affect normal activities [19].

Participants will be excluded if they (1) have any current symptoms related to a structural disease that has been confirmed by endoscopy (e.g., gastrointestinal cancer, eosinophilic esophagitis, candida esophagitis, etc.); (2) have severe dysphagia, hematemesis, weight loss, or hematochezia; (3) have suffered from gastrointestinal cancer during the 5 years before the study begins; (4) have received chemotherapy for cancer during the month before the study begins; (5) have been diagnosed with ischemic heart disease (e.g., angina pectoris or myocardial infarction); (6) have an artificial cardiac pacemaker in the chest; (7) have experienced a hypersensitivity reaction after an acupuncture treatment, or show any other contraindications; (8) are taking part in any other clinical trial that could affect the results of this trial, or are being treated for GERD using any other Korean medical method (a minimum wash-out period of 2 weeks will be required for participation in this trial); (9) have difficulties attending the trial (e.g., serious mental illness, dementia, drug addiction, severe disorders in vision or hearing, illiteracy, time constraints, etc.), and (10) are pregnant or breastfeeding.

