### Withdrawal criteria

Participants will be withdrawn from the study if they (1) miss a scheduled EA treatment three times in a row or (2) take forbidden medication, herbal medicine, or undergo surgery related to GERD during the study period.

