### Drugs forbidden by the study protocol

The following classes of drugs, all of which are used to treat symptoms of GERD, will not be allowed: PPIs, histamine receptor antagonists, prokinetics, mucosal protective drugs, antacids, anti-depressants, antianxiety drugs, lower esophageal sphincter agents, and herbal medicine.

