### Outcome measurement

An independent assessor will give the participants a set of outcome measures; a schedule of these measures is summarized in Table 2.

**Table 2 Tab2:** Study schedule for data collection

Measures	V1	V2	V3	V4	V5	V6	V7	V8	V9	V10	V11	V12	V13
Sociodemographic data	✔												
GERD pattern identification tool	✔												✔
Collection and distribution of diary	✔		✔		✔		✔		✔		✔		✔
Assessment of beliefs in the acupuncture effectiveness	✔												
Adequate relief (AR)		✔	✔	✔	✔	✔	✔	✔	✔	✔	✔	✔	✔
Nepean Dyspepsia Index - Korean (NDI-K)	✔					✔							✔
Numeric rating scale (NRS) for GERD	✔					✔							✔
Korean Gastrointestinal Symptom rating scale (KGSRS)	✔					✔							✔
EuroQol-5 Dimension (EQ-5D)	✔					✔							✔
Perceived Stress Scale-Korean (PSS)	✔					✔							✔
Gut hormones (gastrin and motilin)	✔												✔
Blood collection for cytokine analysis	✔												✔
Qi stagnation and spleen Qi deficiency questionnaire	✔												✔
PGIC GERD symptom						✔							✔
Blinding Index (BI) and cCredibility test													✔
Adverse events investigation		✔	✔	✔	✔	✔	✔	✔	✔	✔	✔	✔	✔
Assessment of concomitant therapy and lifestyle modification	✔	✔	✔	✔	✔	✔	✔	✔	✔	✔	✔	✔	✔
Evaluation of rescue medicines		✔	✔	✔	✔	✔	✔	✔	✔	✔	✔	✔	✔

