##### Gastrointestinal hormone (gastrin, motilin)

GERD is related to weakness in the lower esophageal sphincter [35], and motilin [36] and gastrin [37, 38] have been reported to increase strength of the lower ESP (LESP). Motilin is an endogenous gastrointestinal hormone that increases upper GI tract motility, and it is considered an endogenous prokinetic hormone [39]. Gastrin is also a gastrointestinal polypeptide; it is thought to stimulate the lower esophageal sphincter by increasing the LESP [40]. However, controversy exists regarding whether EA increases gastrin and motilin levels [11, 13–16], so we will attempt to confirm the influence of EA on increases in motilin and gastrin in this trial. Specifically, a nurse will collect a 10-mL blood sample, in which the serum will be separated using a centrifuge. The sample will be analyzed using both a Human Motilin ELISA kit and a Human Gastrin ELISA kit (Mybiosource Inc., San Diego, California, USA). This will be carried out at baseline and visit 12.

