#### Description of baseline characteristics and homogeneity of the two groups

To describe the baseline characteristics of continuous data, the mean ± SD, or range with minimum and maximum, will be used. In the case of dichotomous data, the frequency will be reported as a percentage. To evaluate the homogeneity of the baseline characteristics between the two groups, a two-sample t test for continuous data and the *χ*^2^ test for dichotomous data will be carried out. If there is a significant difference between the two groups in terms of baseline characteristics, we will use analysis of covariance (ANCOVA) or logistic regression.

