#### Secondary outcomes

The independent t test will be used to evaluate changes in the NDI-K score after 6 weeks of treatment. If there is a covariate at baseline, an ANCOVA will be performed. To compare variables between the two groups, the two-sample t test will be used for parametric analyses, and the Mann-Whitney U test, for nonparametric analyses.

A repeated measures analysis of variance or repeated measured ANCOVA will be used to analyze group-by-time interactions, as well as intergroup differences. The *χ*^2^ test or Fisher’s exact test will be used to analyze nominal variables in each group as well as to compare AEs between groups.

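### The only printed wash-out leaves out the conventional GERD drugs that the trial then withholds, so some V1 baselines of secondary outcomes may be taken on, or just after, such a drug

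*Protocol article*

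**What the plan says.** All places are in the protocol article.

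- **Wash-out.** Under Inclusion and exclusion criteria, exclusion 8 concerns people in other trials or who "are being treated for GERD using any other Korean medical method (a minimum wash-out period of 2 weeks will be required". No other wash-out, run-in or drug-free interval is printed.
- **Prior treatment.** Inclusion 5 asks for symptoms that persist despite standard treatment (medication, lifestyle modification or both) "for 4 weeks during the year before the trial begins". It gives no date by which medication must have stopped.
- **Ban.** Drugs forbidden by the study protocol lists classes that "will not be allowed: PPIs, histamine receptor antagonists, prokinetics, mucosal protective drugs, antacids", and further classes including lower esophageal sphincter agents. Withdrawal criteria removes participants who "take forbidden medication, herbal medicine, or undergo surgery related to GERD during the study period". The start of that period is not defined. The Discussion confirms that PPI treatment is withheld.
- **Baselines.** Table 2 (Outcome measurement) takes NDI-K, NRS, KGSRS, EQ-5D, gut hormones and cytokines at V1. For gastrin and motilin the text says "This will be carried out at baseline and visit 12".
- **Adjustment.** Two conditional rules are given: "If there is a significant difference between the two groups in terms of baseline characteristics, we will use analysis of covariance" (or logistic regression), and, for NDI-K, "If there is a covariate at baseline, an ANCOVA will be performed". Neither names recent drug use. Table 2 does schedule "Assessment of concomitant therapy and lifestyle modification" from V1 onward.

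**The concern.** The trial recruits people whose symptoms persist despite standard treatment, so some may still be taking a PPI or a similar drug when they present. If such a person is measured at V1 and then has to stop, the change from V1 to week 6 combines the response to the assigned procedure with the effect of stopping the drug.

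Two things are at stake. First, the change scores compared between arms, such as NDI-K, become noisier. Second, the article intends to read biomarker changes against symptoms: Inflammatory cytokines plans to relate cytokine results to subjective symptoms, and the Discussion plans to correlate objective with symptom outcomes in order to explain mechanism. If stopping a drug moves both a symptom score and a biomarker, it creates an association that has nothing to do with electroacupuncture. Randomization balances the arms on average but does not remove a common cause from a correlation.

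**Working it through.** **Step 1. Does any printed rule require a drug-free interval before V1?** The answer depends on when the study period starts.

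- If it starts after V1, a current user can be measured at V1 while on the drug.
- If it starts at V1, a drug stopped the day before V1 still meets every printed rule.

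On either reading, no interval is required.

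**Step 2. The plan's own figure.** Sample size calculation gives 21.9 per group from responder rates of 92.8% and 57.1%, two-sided 0.05 and 80% power. With the pooled mean rate 0.7495:

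- n = [1.96 × √(2 × 0.7495 × 0.2505) + 0.8416 × √(0.928 × 0.072 + 0.571 × 0.429)]² / 0.357² = 21.91
- 21.9 / 0.75 = 29.2, rounded up to 30 per group

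The figure reproduces and is not in dispute. It concerns the primary outcome only; no power is stated for any secondary outcome.

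**Step 3. Added variance in a change score.** Let p be the share of participants whose V1 value is affected, and d the shift from stopping the drug, in SD of the change score. Neither is in the documents, so both are assumed: p from 10% to 70%, d of 0.2 or 0.5, with d = 1.0 as a sensitivity case.

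- Added variance = p(1 − p)d²
- Effective n per arm = 30 / (1 + added variance)
- Power benchmark: a two-sample t test with 30 per arm, two-sided 0.05, has 80% power at 0.736 SD (noncentral t). Power is then recomputed at 0.736 / √(1 + added variance). This 80% is notional.

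| d | p | Added variance | Effective n | Power |
|---|---|---|---|---|
| 0.2 | 0.1 | 0.0036 | 29.9 | 79.9% |
| 0.2 | 0.5 | 0.0100 | 29.7 | 79.6% |
| 0.5 | 0.1 | 0.0225 | 29.3 | 79.1% |
| 0.5 | 0.3 or 0.7 | 0.0525 | 28.5 | 78.0% |
| 0.5 | 0.5 | 0.0625 | 28.2 | 77.6% |
| 1.0 | 0.1 | 0.09 | 27.5 | 76.5% |
| 1.0 | 0.5 | 0.25 | 24.0 | 70.7% |

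At each d, p = 0.5 gives the maximum.

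**Step 4. Shift in the mean change.** The mean change moves by p × d, equally in both arms on average. At d = 0.5 this is 0.1 × 0.5 = 0.05 SD to 0.7 × 0.5 = 0.35 SD. It cancels in the between-arm difference.

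**Step 5. Spurious correlation.** Suppose stopping the drug shifts both a symptom change and a biomarker change by d, and the two are otherwise unrelated. The induced covariance is p(1 − p)d², and each variance is 1 + p(1 − p)d². At p = 0.5 and d = 0.5 the correlation is 0.0625 / 1.0625 = 0.06. At d = 0.2 it is 0.01 / 1.01 = 0.01. At d = 1.0 it is 0.25 / 1.25 = 0.20.

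**The case against.** The strongest case against has four parts.

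1. **This is silence in a condensed article.** The full protocol and the timeline figure are not shown, and the content of the screening test is not described. The start of a drug ban could be set there. That is possible, and it is why the point is worded as what may happen. But the article does print a wash-out, gives its length and attaches it to a different class of treatment. The defect is in what is fixed.

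2. **Few participants may be affected, and only slightly.** The Abstract and Background describe treatment already undergone, and inclusion 5 accepts lifestyle modification alone. Inclusion 4 requires frequent symptoms in the preceding 7 days, so any current user who enters is still symptomatic on the drug, which limits how far V1 symptom scores can be suppressed. This stands, and favors the lower part of the assumed range for symptom scores. It does not exclude current users, and it says little about hormones or cytokines.

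3. **No within-arm before/after test is planned.** Correct: the analysis section plans between-group tests and group-by-time interactions. A reader might infer that the planned tests are confounded by drug withdrawal. They are not, since randomization balances it on average. What remains is chance imbalance, noise and the intended symptom-biomarker relation.

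4. **The 2 weeks are borrowed and have a cost.** Nothing in the article supports 2 weeks for these drugs, and symptomatic patients would go longer without treatment. This stands and shapes the fix.

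A reader might also infer that the primary outcome is compromised. Adequate relief is first asked at V2, each time relative to the last visit, and no V1 score enters it.

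**Conclusion.** The point holds in a limited form. As printed, entry does not require any interval off conventional GERD drugs before V1, so on-drug or just-off-drug baselines of secondary outcomes are possible. How many would occur is unknown.

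The size is modest. For shifts of 0.2 to 0.5 SD and 10% to 70% users, added variance is about 0.4% to 6%, and a notional 80% power falls to between 79.9% and 77.6%. A spurious symptom-biomarker correlation would be at most about 0.06 if both measures shift equally. User share, shift and the 80% benchmark are all assumptions. Larger shifts are possible, but the documents offer no support for them, so the 1.0 SD rows are a sensitivity case and not a bound.

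The planned adjustments do not reliably repair this: one waits for a significant baseline difference and the other names no covariate. This is a cheap improvement to the secondary and mechanistic results and poses no threat to the primary comparison.

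**What to change.** **Preferred.** Amend exclusion 8 so that the wash-out also covers the GERD drugs listed under Drugs forbidden by the study protocol, for 2 weeks or another interval that the sponsor justifies. Take V1 questionnaires and blood only once it is met, and allow the rescue medicine during it. The cost is one amended criterion, a short delay before V1, and about 2 more drug-free weeks for current users.

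**If the wash-out is not adopted.** Prespecify use of a listed GERD drug at V1 (yes/no) as a covariate in the secondary comparisons, in place of the adjustment triggered by a significant baseline difference. Table 2 already collects concomitant therapy at V1, so this costs one degree of freedom and no new data. With the wash-out in place, the covariate would be largely redundant.

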### Recruitment

We will advertise the study on the notice boards and the homepage of the hospital, as well as in local newspapers, and the investigators who are Korean medical doctors, will obtain informed consent from all participants. Specifically, two written informed consent forms (a general consent form and an additional consent provision for the collection and use of the participants’ biological material) will be given to the participants. After the participants sign the forms voluntarily, the participants will go through the screening test. We will provide a copy of the consent form and other related documentation to the participants upon request.

#### Randomization and allocation concealment

Sixty participants will be randomly assigned to either the EA or sham EA group. A random number table will be generated using block randomization with blocks of four by R for windows 3.2.1 (R Foundation for Statistical Computing, Vienna, Austria); to this end, the block randomization function will be used with blocks of four. The allocations will be kept sealed in a double-locked cabinet by an independent statistician. If the participants pass the screening test, they will be allocated according to the procedure above to conceal the allocation from both investigators and participants. After allocation, the statistician will email a unique random number and participant group allocation to both the clinical research coordinator and the Korean medicine doctors (KMDs). This feedback document will be kept in the master file for the trial.

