### Blinding

In this study, the participants, the outcome assessors, and the data managers, including the statistician, will be blinded to the group allocation. The acupuncture practitioner will not be blinded because of the characteristics of the Park sham device. The investigators will not give any clues to the participants regarding group allocation, nor will the participants from one group meet those from the other group. To evaluate the success of blinding, a blinding index will be assessed after the participants’ final treatment. Blinding will be maintained until the study is finished. However, if a serious adverse event (AE) occurs, blinding will be lifted, and investigators will notify the participant involved of his/her group allocation in accordance with the standard operating procedures (SOPs).

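### One fixed block size of four at a single centre, with each allocation emailed to unblinded doctors and no stated separation from those who consent, leaves about a third of assignments deducible

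*Protocol article*

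**What the plan says.** The section Randomization and allocation concealment in the protocol article gives the sample and the method: "Sixty participants will be randomly assigned to either the EA or sham EA group", and "A random number table will be generated using block randomization with blocks of four by R for windows 3.2.1". The same sentence repeats the size: "the block randomization function will be used with blocks of four". No second block size and no stratification factor is mentioned. An independent statistician keeps the list locked away, and a participant is allocated only after passing screening. The section gives concealment from investigators as well as participants as the purpose of this procedure.

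The section then describes release of the result. After each allocation, "the statistician will email a unique random number and participant group allocation to both the clinical research coordinator and the Korean medicine doctors (KMDs").

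Four other statements bear on the point:
- Design: "A single-center, parallel, randomized, patient-blinded, assessor-blinded, sham EA-controlled trial will be conducted".
- Blinding: "The acupuncture practitioner will not be blinded because of the characteristics of the Park sham device".
- Table 1, practitioner background: two Korean medicine doctors give the treatment.
- Recruitment: "the investigators who are Korean medical doctors, will obtain informed consent from all participants". Screening follows consent.

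The article does not say whether the doctors who consent are the doctors who receive the emails, who applies the screening test, or whether the block size is withheld from site staff.

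**The concern.** A locked list stops future entries from being read. It does not stop them from being worked out. With two places per arm in every block of four, anyone who counts past allocations knows the fourth assignment, and knows the third as well when the first two went to the same arm. The coordinator and the doctors are sent the information needed for that count.

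The harm would arise at entry. Eligibility depends partly on judgement: the required number of symptom days depends on whether symptoms are graded mild or moderate, time constraints are a ground for exclusion, and participants are included on history without gastroscopy. A person who expects a particular arm next could bring a candidate forward or put one back without breaking a rule. The arms could then differ in prognosis from the start, and the comparison of responder proportions would carry that difference. Blinded participants and assessors protect how the outcome is measured. They do not protect who enters which arm.

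**Working it through.** **Inputs.** Block size 4, 60 participants and 30 per group come from the article. One unstratified list is assumed, because the article names one centre and no stratification factor.

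**The plan's own figures.** The article states no predictability figure. Its allocation figures agree with each other: 60 / 4 = 15 complete blocks, each 2 + 2, giving 15 × 2 = 30 per group as stated.

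**Certain assignments per block.** There are 6 equally likely orders of two A and two B. An assignment is certain once one arm has used both its places.
- AABB and BBAA: the third and fourth are certain, so 2 each.
- ABAB, ABBA, BAAB and BABA: only the fourth is certain, so 1 each.
- Mean: (2 × 2 + 4 × 1) / 6 = 8/6 = 1.333 per block, or 1.333 / 4 = 33.3%.

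**Over the trial.** The expected number is 15 × 1.333 = 20 of 60. The number in a given list is 15 + K, with K binomial (15, 1/3). The possible range is 15 (25%) to 30 (50%). The probability of 17 to 23 is 0.9692 − 0.0194 = 0.95. The last place of every block, 15 of 60, is always certain.

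**Best guess.** The observer guesses the arm with more places left, and tosses a coin when the two are equal.

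| Place in block | P(certain) | P(correct guess) |
|---|---|---|
| 1 | 0 | 0.500 |
| 2 | 0 | 0.667 |
| 3 | 1/3 | 1/3 × 1 + 2/3 × 0.5 = 0.667 |
| 4 | 1 | 1.000 |
| Mean | 0.333 | 2.833 / 4 = 0.708 |

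Without information the guess is right 50% of the time.

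**Effect of varying the block size.** 4,000 lists of 60 were simulated. The observer knows which sizes are in use, but not their order, and updates by Bayes' rule. The fixed-four row checks the method against the exact values.

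| Block sizes | Certain, mean of 60 | Share | Correct guess |
|---|---|---|---|
| 4 only | 20.0 | 33.3% | 70.8% |
| 4 and 6 | 3.3 | 5.5% | 69.1% |
| 4, 6 and 8 | 1.4 | 2.3% | 67.8% |

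A larger fixed block does much less. By the same enumeration, a fixed 8 still leaves 1.6 / 8 = 20% certain. It is the random variation that removes certainty. Better-than-chance guessing falls by only 70.8 − 67.8 = 3.0 percentage points, so this change alone is not enough.

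**The case against.** The strongest objection is that the link to enrolment is inferred. The article says that Korean medical doctors obtain consent and that Korean medicine doctors receive the allocations. A shared profession is not a shared role. Role separation is also the kind of detail that an article may leave to the full protocol or to the operating procedures it cites. This stands, and it is why the point is conditional.

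A reader might infer three stronger things, none of which the article supports:
- **That concealment fails, with a third of assignments known to the recruiters.** No section says that those who consent or screen see past allocations or know the block size. One third is also an average over lists, and it applies only to someone who follows the whole sequence.
- **That the damage could not be repaired.** The section on baseline characteristics plans covariance analysis or logistic regression if the groups differ significantly. That can address measured imbalance. It cannot reach unmeasured selection, and it depends on a significance test with 30 per group.
- **That a patient-reported primary outcome makes the problem worse.** This confuses measurement with selection. Participants are blinded, and a blinded assessor separate from the treating doctors collects the outcomes.

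The existing safeguards also count: an independent holder of the list, allocation only after screening is passed, and release only after allocation. They close direct reading of the list and leave deduction as the remaining route.

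**Conclusion.** The point holds as an avoidable weakness in a procedure whose stated purpose includes concealment from investigators. The arithmetic is firm: on average 20 of 60 assignments are deducible with certainty, and guesses are right about 71% of the time.

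Those figures rest on three assumptions: one unstratified list, an observer who sees the sequence in order, and an observer who knows the block size or works it out. Bias needs a fourth, that this observer also influences consent, screening or timing. The article neither states nor rules out the last three, but it sends the sequence to the coordinator and the doctors and describes nothing to keep it from those who enrol. Predictability is an opportunity for selection bias and not evidence that it occurs. The sample size and the choice of primary test are unaffected.

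**What to change.** Make two changes together.

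1. Generate the list with randomly varying block sizes, for example 4, 6 and 8, and do not disclose the sizes to site staff. Recruitment was due from August 2015, so if enrolment has begun, apply this to the unused part of the list, starting after a completed block.
2. Send each allocation only to the doctor treating that patient, and not to staff who consent or screen. State in Recruitment and in Randomization and allocation concealment who consents, who screens and who receives allocations. If these roles are already separate, one sentence saying so answers most of the concern.

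The second change is needed because the first removes most of the certainty but little of the better-than-chance guessing.

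The cost is a new list, a changed email route and a possible final imbalance. If entry stops halfway through a block of 8 after four assignments to the same arm, the groups differ by 4 patients, and that is the most they can differ.
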